# 6. Investigational therapy and controls

## 6.1 Acupuncture

A total of 12 treatments over 3 menstrual cycles will be administered according to the frequency specified in the subjects’ group allocation. The study acupuncturists will include the primary investigator ([name]) and all study acupuncturists will be experienced, with a minimum of a Bachelors level qualification in Acupuncture and will hold a current annual practicing certificate with a relevant professional acupuncture body. Practitioners will be located in Auckland and Wellington, New Zealand. [name] will also be involved in training and quality control of other study acupuncturists.

Following the first phase of this mixed methods PhD thesis a trial protocol has been developed based around using a manualised version (50) of standard acupuncture treatments which has been designed in consultation with experienced practitioners through interviews and focus groups.

This manualisation allows considerable flexibility, in order that the treatment can match patient variability. The protocol is not too broad, such that “anything goes” as this would mean that it would be more difficult to attribute any impact of treatment to the different interventions we are using, frequency and stimulation of treatment. The protocol is also not too narrow, as we want the treatments to reflect how acupuncturists normally work in clinical practice. This is an important consideration in designing a clinically relevant intervention (25).

The rationale for the individualization of treatments is based on the TCM principle of “*Yi bing tong zhi, tong bing yi zhi*” translated to mean “Different diseases, same treatment. Same disease, different treatment” (pp2) (53). To allow for this important component of TCM’s theoretical framework to be preserved, clinicians will take a history and give a TCM diagnosis during the first session. This will be guided by key diagnostic factors that have been stressed by experienced clinicians. Once a TCM diagnosis has been ascertained then practitioners will have flexibility in their point selection for this pattern. Each pattern has a selection of ‘vital’ points that have been identified by expert practitioners as being vital to the treatment outcome for each pattern. At least 3 of these ‘vital’ points will need to be used in each treatment session. Practitioners will then be able to choose from an optional list of points for each pattern that can be used as desired. Other common co-interventions such as moxibustion, a warming therapy often used in the treatment of gyanecological complaints due to ‘cold’, are also allowed (54). Herbal medicine or additional supplementation is not to be provided by practitioners during the trial. Each subsequent treatment session will allow for a confirmation or update on the TCM diagnosis and therefore point selection may be varied from treatment to treatment.

Acupuncture points will be needled bilaterally except those where only one side is used clinically such as opening extraordinary vessels such as the Chong Mai (54). Stimulation parameters are detailed in the group assignments. Point location and needling depth will be as specified in *A Manual of Acupuncture* (55). Practitioners will maintain logbooks detailing all aspects of treatment provided (including co-interventions such as moxibustion). Single use, stainless steel needles of varying gauge (.20 x 30mm or .25 x 40mm), dependent on body shape, will be used.

After the conclusion of the 3 menstrual cycles there will be an approximately one-month follow up period ending on the completion of the subjects subsequent menstrual period.

## 6.2 Control group

There is no control group in this study as it is designed to examine the differing contribution of different acupuncture components to the clinical outcome.

## 6.3 Prior and Concomitant Medications

### 6.3.1 Permitted medications

Subjects will continue with all prescribed medication and can use analgesics as needed for pain relief.

# 7. Study Assessments

## 7.1 Safety Assessments

At each treatment session the treating acupuncturist will ask the participants if they have had any adverse events or reactions after the last treatment. Any adverse events or reactions that are thought to be causally associated with the intervention will be recorded in the practitioners log book and reported to the primary investigator [name]. Any adverse events reported to the PI will be discussed with the supervisory panel and assessed for clinical significance. All adverse events reported during the duration of the trial (including follow-up) will be recorded under adverse events as part of the case report form.

Participants during the interviews will also be asked about any adverse events or unpleasant experiences during the trial.

Minor adverse events for acupuncture and moxibustion are expected to occur at a rate of around 1.3 per 1,000 treatments (56) and mostly include local pain on needling, mild bruising and bleeding (57). The risk of burns from moxibustion is very rare (56-58).

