A typical acupuncture consultation includes but is not limited to: history taking, self care and lifestyle advice, TCM diagnosis and explanation, palpation of the pulse and other parts of the body, observation of the tongue, insertion and manipulation of needles, as well as common co-modalities such as moxibustion and cupping (23,29,30).

There is some evidence that the advice given during the acupuncture treatments and the way that the advice is delivered is an important component of the clinical outcome, however its role in outcomes in the treatment of dysmenorrhea is unclear (31-33).

*Acupuncture treatment of Dysmenorrhea*

The most recent systematic reviews have found conflicting results in the effectiveness of acupuncture in the treatment of dysmenorrhea (34).

One large scale pragmatic trial (35) showed a significant reduction in menstrual pain and an increase in quality of life in women undergoing acupuncture treatments over a three month period compared to women having only usual care. This trial did not document components of the treatment or frequency of treatment and therefore it is impossible to determine what components of the acupuncture treatment contributed towards the positive outcome. There is conflicting evidence in the literature on role of dosage and stimulation style in improving clinical outcomes of acupuncture treatment of dysmenorrhea. Chinese based literature shows very positive results with higher frequency of treatment (36-39) and with the usage of electroacupuncture (40-43). However these are tempered by poor methodological quality (44) and by acupuncture treatments that do not represent clinical practice in Australia and New Zealand (unpublished data from thesis) and other western countries (45).

In addition to measuring outcomes for symptoms of dysmenorrhea women who complete the trial will be invited to take part in semi-structured interviews that will examine the acceptability of the differing interventions, the importance of the explanations and advice given by the practitioners as well as their experience in the trial itself.

*Methodological challenges:*

Recent papers from CAM experts (46) acupuncture researchers (29,47)and acupuncture practitioners (45,48) all emphasise the vital need for research to reflect and inform clinical practice.

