5.5.2 Treatment allocation

Randomization will be into one of four study groups:

High Frequency – Manual stimulation: Women randomly allocated to this group will receive 3 acupuncture treatments in the 7 days prior to menses and 1 acupuncture treatment in the first 3 days of menses. Stimulation will be provided by manual acupuncture, achieving DeQi upon needle insertion. Subsequent stimulation based on practitioners differential diagnosis. Needles will be retained for 20-30 minutes

High Frequency – Electro acupuncture stimulation: Women randomly allocated to this group will receive 3 acupuncture treatments in the 7 days prior to menses and 1 acupuncture treatment in the first 3 days of menses. Stimulation will be provided by Electro-Acupuncture, achieving DeQi upon needle insertion. Subsequent stimulation will be using a 2/100Hz waveform for 20-30 minutes.

Low Frequency – Manual Stimulation: Women randomly allocated to this group will receive 3 acupuncture treatments in the 3 weeks prior to menses (1/week) and 1 acupuncture treatment in the first 3 days of menses. Stimulation will be provided by manual acupuncture, achieving DeQi upon needle insertion. Subsequent stimulation based on practitioners differential diagnosis.Needles will be retained for 20-30 minutes

Low Frequency – Electro acupuncture stimulation: Women randomly allocated to this group will receive 3 acupuncture treatments in the 3 weeks prior to menses (1/week) and 1 acupuncture treatment in the first 3 days of menses. Stimulation will be provided by Electro-Acupuncture, achieving DeQi upon needle insertion.Subsequent stimulation will be using a 2/100Hz waveform for 20-30 minutes.

5.5.3: Withdrawal procedures

If a participant wishes to withdraw from the trial they will be immediately removed from treatment. The most recent menstrual pain diary will be used and they will be requested to complete an SF-36.

If a participant withdraws during intervention they will not be replaced however if they withdraw post randomization but prior to the first treatment they will be replaced.

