11.2.2 Emergency contact with Investigators

All participants will be given emergency contact numbers of both the study acupuncturists and the primary investigator [name]

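### Events judged unrelated to acupuncture have no stated route into the safety record, and no systematic adverse-event enquiry is stated after a woman's last session

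*Protocol*

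**What the plan says.** Protocol Section 7.1 sets out four steps.

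- **Enquiry at sessions.** "At each treatment session the treating acupuncturist will ask the participants if they have had any adverse events or reactions after the last treatment". The question is open and is not limited to events linked to treatment.
- **Log book and escalation.** "Any adverse events or reactions that are thought to be causally associated with the intervention will be recorded in the practitioners log book". The same sentence sends those events to the primary investigator. Events that reach the investigator are discussed with the supervisory panel.
- **Case report form.** "All adverse events reported during the duration of the trial (including follow-up) will be recorded under adverse events as part of the case report form".
- **Interviews.** "Participants during the interviews will also be asked about any adverse events or unpleasant experiences during the trial". Section 1.1 says who is interviewed: "women who complete the trial will be invited to take part in semi-structured interviews".

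Other sections bear on the period after treatment.

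- Section 11.2.2: "All participants will be given emergency contact numbers of both the study acupuncturists and the primary investigator".
- Section 5.5.3, on withdrawal: "The most recent menstrual pain diary will be used and they will be requested to complete an SF-36". It mentions no adverse-event enquiry.
- Section 7.2 describes the 1, 6 and 12 month contacts as pain diaries.
- Section 8 lists the diary content and gives no adverse-event item. The exit questionnaire covers satisfaction and the components of treatment.

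**The concern.** A judgement about cause comes before recording. The practitioner asks about everything, but only what is believed to be due to the treatment goes into the log book and on to the investigator. The panel cannot review an opinion on an event it never sees.

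Attribution is difficult in this population. Section 1.1 names headaches, nausea and vomiting as features of primary dysmenorrhea, and Section 8 has the diary record headache and vomiting as secondary symptoms. Such an event after a treatment can easily be put down to the condition and left out of the safety record.

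The second issue is coverage in time. An enquiry tied to the next session cannot reach beyond the last one, and a woman who stops because of an adverse event has no stated enquiry at all. Section 7.1 nevertheless says that follow-up is covered. An event never recorded cannot be recovered at analysis, so this has to be settled in the protocol and not in a later analysis document.

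**Working it through.** No figure in the protocol is in dispute. The check sets the passages side by side, with simple arithmetic for scale.

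**1. Route of an event mentioned at a session (Section 7.1)**

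| Event | Log book | Primary investigator | Panel | Case report form |
|---|---|---|---|---|
| Thought causal | Yes | Yes | Yes | Yes |
| Thought unrelated | Not provided for | Not provided for | Not reached | Covered by the rule if it counts as reported, but no route stated |

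The case-report-form sentence turns on what counts as reported.

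- If it means events that passed the filter, the word all promises more than is collected.
- If it means everything women mention, the log-book rule does not supply it.

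Both readings need an edit. Section 10.1 does not close the gap, because the management meetings discuss events that the study acupuncturists report.

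**2. Who is asked, and when**

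| Time | Stated enquiry of all women |
|---|---|
| Sessions 2 to 12 | Yes, about the interval since the previous treatment |
| After treatment 12 | None stated |
| Contacts at 1, 6 and 12 months | None stated (pain diary) |
| Withdrawal | None stated (last diary and SF-36) |
| Interview | Completers who accept; timing not given |
| Emergency numbers | All women, but only if the woman calls |

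**3. Scale of the final-treatment gap**

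Inputs: 68 women (Section 4.1), 12 treatments each (Section 6.1), and about 1.3 minor events per 1,000 treatments (Section 7.1).

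- Planned treatments: 68 x 12 = 816.
- Expected minor events in the whole trial: 816 x 1.3 / 1,000 = 1.06.
- Treatments with no later session: 68, one per woman. 68 / 816 = 8.3%.
- Expected minor events from those: 68 x 1.3 / 1,000 = 0.09.

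This assumes that every woman has all 12 treatments. Section 9.1 predicts 10% loss. A woman who stops early also has one last treatment with no later session, so the count of 68 holds as long as each woman is treated at least once.

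**4. Scale of the filter**

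This cannot be derived. The protocol does not say how many session-reported events would be judged unrelated. The rate of 1.3 per 1,000 is for minor events of acupuncture and moxibustion, so it does not bound events from other causes. With about one minor event expected, a few unrecorded events would change the safety result.

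**The case against.** The strongest defence is that the two sentences in Section 7.1 govern different records. On that reading the scheme has two tiers: escalate what looks related, and put everything reported on the case report form. The log book, case report form and diary are not shown and may supply the missing step. This has force. A reader might infer a flat contradiction, and the text does not support that. What remains is that the protocol states a restrictive rule for the session record and no route around it.

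A reader might also infer that women are asked only at the next session, or that everything after the last treatment is lost. Neither holds. The interviews ask about any adverse events with no causality filter, the case-report-form rule names follow-up, and every woman has emergency numbers. These routes are partial, because interviews reach only completers who accept and telephone reports are spontaneous.

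Two further points stand. Section 7.1 does not name who judges causality. The treating practitioner is the natural reading, since the filter governs the practitioner's own log book and comes before the report to the investigator, but it is an inference. And the minor events that Section 7.1 expects, such as bruising or bleeding at the needle site, may be evident during the session itself, which makes the final-treatment gap smaller still.

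**Conclusion.** The point holds in a limited form. Log-book entry, reporting to the primary investigator and hence panel review are restricted to events thought causal. No systematic enquiry of all women is stated after the last session, at the follow-up contacts or at withdrawal. The stated recording of all reported events, follow-up included, is therefore not secured.

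Adverse events may be under-recorded, and the record may depend on an unreviewed opinion, probably the treating practitioner's. A reader might infer that counts will certainly be too low. The documents do not show that, because the number filtered out is unknown and the partial routes may recover some events. The filter is the main weakness. The final-treatment gap alone is about 0.09 of about 1.06 expected minor events, if the protocol's rate applies and all 816 treatments are given.

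The primary pain comparison is unaffected. The change is worth making because it is cheap and the loss cannot be repaired later.

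**What to change.** - **Section 7.1, recording.** Replace the filtered rule with one under which every reported adverse event or reaction is entered in the log book and the case report form, whatever its suspected cause.
- **Section 7.1, causality.** Hold causality as a separate field. State who completes it, and have the primary investigator and supervisory panel review it.
- **Sections 7.2 and 8, diary.** Add one adverse-event question to each menstrual diary, including the diary after the final treatment and the follow-up diaries at 1, 6 and 12 months.
- **Section 5.5.3, withdrawal.** Ask the same question at the withdrawal contact.

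The cost is revised log-book wording and one diary question. The downside is more minor, unrelated events to record and review.

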## 7.2 Study assessments

The menstrual pain diary will be used to assess primary and secondary endpoints at baseline and at the end of every menstrual period during the 3 month study period. Follow-up pain diaries will also be collected at 1, 6 and 12 months post trial completion.

The SF-36 will be assessed at baseline and then at 1 month post trial completion.

Patient satisfaction with the trial will be assessed at the end of the trial with an exit questionnaire given after the final acupuncture treatment.

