# 2. Study Objectives

The primary aim of this project is to examine the effect of changing frequency and type of stimulation on the symptoms of primary dysmenorrhea.

The specific questions that this project address are:

1. Does using a manualised protocol based on current clinical experience provide a positive outcome with symptoms of primary dysmenorrhea?
2. What extent do differing frequencies of treatment and types of stimulation contribute to that effect?
3. Is acupuncture, especially in more frequent treatments, an acceptable intervention for participants ?
4. Does TCM acupuncture change study participants perceptions of health and illness with respect to dysmenorrhea ?
5. What other components of the acupuncture treatment are important to study participants ?

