## 5.4 Ineligible and non-recruited participants

Women who do not meet the initial eligibility criteria or whose menstrual pain diaries do not meet eligibility criteria will be logged. Women who decline to participate after initial contact will also be logged, with a reason for declining (if given).

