# 8. Data Collection

The primary investigator, [name], will be responsible for collection of these outcomes at baseline, after each subsequent menstrual period during the trial phase and then again at one, six and twelve months post trial completion.

Baseline data includes age, ethnicity, height, weight, age of menarche, onset of dysmenorrhea, length of menstrual cycle, length of menstrual period, smoking status, alcohol consumption, baseline analgesic usage and self reported dysmenorrhea symptoms and severity. A 5 point Likert scale will assess prior belief in acupuncture’s effectiveness.

*Primary outcome measure:*

Numerical rating scale (NRS) for pain. Each subject will keep a menstrual diary provided by the researcher. This will note the day of menses, average and maximum pain per day on an 11 point NRS with 0 being no pain and 10 being the worst pain imaginable. NRS is used in preference to VAS as it is comparable (59) but has a higher compliance rate, is easier to use and fits the compact format of a menstrual diary (60). The primary endpoint is a 20% difference in NRS rated average pain severity between groups.

*Secondary outcome measures:*

Secondary outcome measures which will be captured by the menstrual diary are duration of menstrual pain (hours), menstrual characteristics (flow, clots), painkillers taken (type, dosage, number of doses), non pharmacological interventions (heat,rest) and secondary symptoms of dysmenorrhea (headache, vomiting etc).

HRQoL will be recorded by the Short Form Health Survey (SF-36) at two time points; baseline and at the one month follow-up. The SF-36 has been shown to be valid and reliable across a range of populations (61,62) and has shown suitability for use in dysmenorrhea (63).

An exit questionnaire will be used to determine patient satisfaction with the different interventions and examine which components of the consultation and treatment sessions were important.

*Quality assurance:*

Quality assurance measures on needling technique and point selection will be carried out on practitioners during the study period by using an independent acupuncturist to check point selection and location at least once for each practitioner. Needling technique will be measured using a newly validated tool, the AcuSensor (64).

*In-depth interviews:*

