# 9. Statistics and Data Analysis

## 9.1 Sample Size calculation:

This trial is designed to demonstrate a 20% difference in average pain intensity between groups as measured by the Numeric Rating Scale (NRS). Based on previous study data (65) a standard deviation of 1.3 units on a pain scale was used. An alpha of .05 and power of 90% gives a total sample size of 60 women. Previous studies (35,65) have had relatively low loss to follow-up (~10%) therefore a sample size of 68 women will be used to account for the predicted loss to follow-up of 10%.

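### Women who withdraw are not asked about acceptability, so the answer to research question 3 is likely to be too favourable, particularly for the high-frequency schedule

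*Protocol*

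**What the plan says.** Protocol section 2 lists five research questions. The third is: "Is acupuncture, especially in more frequent treatments, an acceptable intervention for participants". Two instruments bear on it.

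- **Interviews.** Section 1.1 says that "women who complete the trial will be invited to take part in semi-structured interviews that will examine the acceptability of the differing interventions".
- **Exit questionnaire.** Section 8 says: "An exit questionnaire will be used to determine patient satisfaction with the different interventions". Section 7.2 sets the timing: "Patient satisfaction with the trial will be assessed at the end of the trial with an exit questionnaire given after the final acupuncture treatment". Section 6.1 sets the full course at 12 treatments over three cycles.

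For a woman who withdraws, section 5.5.3 says: "The most recent menstrual pain diary will be used and they will be requested to complete an SF-36". It mentions no exit questionnaire, interview or reason for leaving. The same section distinguishes women who leave during the intervention, who are not replaced, from those who leave earlier: "if they withdraw post randomization but prior to the first treatment they will be replaced".

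Section 5.4 logs reasons only for women who decline after first contact, not for randomised women who leave. Section 6.1 has practitioners keep logbooks of the treatment given, and section 10.1 has compliance and retention discussed at management meetings.

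**The concern.** Whether a woman finishes the course depends partly on whether she finds it acceptable. If only finishers are asked, the respondents are selected on something that the answer itself affects, and the usual direction of the error is towards too favourable a result.

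The risk is greatest for the schedule that question 3 singles out. Section 5.5.2 puts three visits into the 7 days before menses in the high-frequency arms, against one a week for three weeks in the low-frequency arms. If the denser schedule leads more women to stop, the comparison of acceptability between schedules is distorted as well as its level.

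The replacement rule adds to this. A woman who leaves on learning her allocation supplies no acceptability data, and her place goes to another participant.

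This concerns who is asked and when, which the protocol fixes. Views and reasons that were never collected cannot be recovered at the analysis stage.

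**Working it through.** **The plan's own figure.** Section 9.1 starts from 60 women and states that "a sample size of 68 women will be used to account for the predicted loss to follow-up of 10" per cent. 60 / (1 − 0.10) = 66.7, which rounds up to 67. By arm, 15 / 0.90 = 16.7, which rounds up to 17, and 4 × 17 = 68. The stated total reproduces.

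**Inputs.**
- Women per frequency level: 2 × 17 = 34 (section 4.1).
- Proportion leaving, d: 10% as the central value, borrowed from section 9.1. That figure is loss to follow-up, not withdrawal from treatment, so using it here is an assumption. Range shown: 5% to 20%.
- Proportion of completers who find the schedule acceptable, c: assumed 90% or 80%. The protocol gives none.
- Proportion of leavers who find it acceptable, l: assumed 0% or 50%. The protocol gives none.

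**Formula.** Acceptability among all randomised women = (1 − d) × c + d × l. A completers-only result gives c, so the overstatement is d × (c − l). It is zero if leavers think as completers do.

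**Women missing.** At d = 10%, 34 × 0.10 = 3.4 women per frequency level.

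**Overstatement in percentage points.**

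| d | c = 90%, l = 0% | c = 90%, l = 50% | c = 80%, l = 0% | c = 80%, l = 50% |
|---|---|---|---|---|
| 5% | 4.5 | 2 | 4 | 1.5 |
| 10% | 9 | 4 | 8 | 3 |
| 20% | 18 | 8 | 16 | 6 |

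For example, at d = 10%, c = 90% and l = 0%: 0.90 × 0.90 = 81%, against 90% among completers. With l = 50%: 0.90 × 0.90 + 0.10 × 0.50 = 86%.

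**Unequal withdrawal, as an illustration.** Take 15% in high frequency and 5% in low frequency, which averages 10%, with 90% of completers satisfied in both.
- If no leaver finds the schedule acceptable: 0.85 × 0.90 = 76.5% against 0.95 × 0.90 = 85.5%, a difference of 9 points.
- If half of the leavers do: 0.765 + 0.15 × 0.50 = 84% against 0.855 + 0.05 × 0.50 = 88%, a difference of 4 points.

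Completers alone would show no difference in either case. In women, the split is about 5 (34 × 0.15 = 5.1) against 2 (34 × 0.05 = 1.7).

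**The case against.** **The questionnaire is not expressly limited to completers.** The final treatment could mean each woman's own last session, and section 8 sets no such limit. This stands as a possible reading. However, section 7.2 also places the questionnaire at the end of the trial, and section 5.5.3 lists what is requested at withdrawal without naming it. Completers only is the more natural reading, though it is inferred.

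**The interview limit rests on one sentence in the Background.** The in-depth interview text in section 8 opens abruptly and does not say who is invited, so wording may be missing from the public copy. That lowers confidence about the full interview plan, but the sentence in section 1.1 is explicit and nothing available contradicts it.

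**Leavers are not invisible.** A reader might infer that they are never counted. The documents do not support that: logbooks and retention reviews would show withdrawals and attendance by arm. What is missing is the leavers' own views, their reasons, and any stated use of attrition to answer question 3.

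**Completers can be critical too.** A reader might infer that the trial is bound to report similar, high satisfaction in every arm. Nothing in the protocol implies this. The interviews cover negative as well as beneficial aspects (section 8), and women who finish a demanding schedule may still say that they disliked it.

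**The percentages are assumed, and the component is largely qualitative.** Both are true. Interviews are analysed thematically (section 9.2), and no acceptability percentage is a planned output. Counting every leaver as dissatisfied is the extreme case, since women also leave for unrelated reasons. The figures show only how large the error could be. A thematic account drawn only from those who stayed has the same selection.

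**Conclusion.** The point holds in a limited form. On the most natural reading, the plan does not seek the views of women who withdraw on acceptability, and it does not use the withdrawals it will know about to answer question 3. Acceptability is therefore likely to be overstated, particularly for the high-frequency schedule.

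With 10% leaving and 90% of completers satisfied, the overstatement is about 4 to 9 points, depending on whether half or none of the leavers find the schedule acceptable. It would be larger with more withdrawal, and it could differ between arms if withdrawal does. All the acceptability rates, the use of 10% as a withdrawal rate, and the unequal split are assumptions. The direction is likely rather than certain: it requires leavers to be less satisfied than completers.

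This affects one of the secondary questions. The primary NRS comparison and the sample size do not depend on it. The change is worth making because it is cheap and serves a stated aim.

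**What to change.** - In sections 5.5.3 and 7.2, offer the exit questionnaire, with an item on the reason for leaving, and the interview invitation to every randomised woman, at withdrawal or after her last treatment. Include women who leave before the first treatment and are replaced.
- Bring the interview sentence in section 1.1 into line.
- State that withdrawals and the number of the 12 sessions attended will be reported by randomised frequency arm, alongside the satisfaction and interview results, as part of the answer to question 3.

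The cost is one extra form at withdrawal and some rewording. The questionnaire already exists, women who withdraw are already approached for an SF-36, and the logbooks supply the session counts. Some leavers will decline or be out of reach, so the bias is reduced but not removed, and the number of leavers who did not respond should be reported. No treatment schedule or clinical rule changes.
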